**Methods/design:**

The ROPISIO study is a two-center, randomized, double-blind, placebo-controlled trial being conducted in La Roche sur Yon and Nantes, France. It will involve 272 women with vaginal singleton delivery and mediolateral episiotomy at term (≥ 37 weeks). Perineal infiltration (ropivacaine 75 mg or placebo) will be administrated just after vaginal birth and before episiotomy repair. The primary outcome will be the analgesic efficacy at day 7 postpartum (midterm), defined by the Numeric Pain Rating Scale (NPRS) strictly superior to 3/10 on the perineal repair area. Secondary outcomes will be the analgesic efficacy (NPRS) and the impact of pain on daily behavior, on the quality of life (36-item Short Form Health Survey), on the occurrence of symptoms of postpartum depression (Edinburgh Postnatal Depression Scale), and on sexual health (Female Sexual Function Index) at 3 and 6 months (long-term) using validated online questionnaires. This study will have 90% power to show approximately 30% relative risk reduction in the incidence of perineal pain at day 7, from 70.0% to 50.0%.

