### Randomization

The randomization will be centralized and stratified by center and parity and will be performed according to a 1:1 ratio. The randomization will be performed by nonvarying size block. A computer-generated randomization list will be carried out by a statistician before the study begins. Once a woman has been included through the filing of an electronic case report form (eCRF) directly via the internet (Clinsights software; Glassbeam, Santa Clara, CA, USA), she will retain her randomization number (if it has been assigned to her) even if she withdraws from the study or refuses randomization afterward.

Women will be randomized after episiotomy and before the beginning of the suture to receive either 75 mg of ropivacaine (Fresenius Kabi, Sèvres, France; marketing authorization number 3400957740832 [2009, RCP rev. 08/09/2016]) in a 20-ml syringe (10 ml of ropivacaine 7.5 mg/ml and 10 ml of normal saline) or 20 ml of placebo (normal saline; Fresenius Kabi, Sèvres, France; marketing authorization number 34009415 73941). The randomization list will be created by La Roche sur Yon Clinical Research Unit and transmitted to the pharmacy department of Nantes University Hospital, which will prepare the blinded products. Numbered and identically labeled boxes with the study number will be produced. Each box will contain a 20-ml vial of the study drug (ropivacaine or placebo according to the randomization number). The syringe will be prepared in a specific room outside the delivery room by a midwife or an anesthetist not directly involved in patient management. A label “ROPISIO Study” and the randomization number will be located on the syringe without any information about the product (ropivacaine or placebo) inside. Then, the syringe will be given to the clinician who will be performing the suture of the episiotomy. Thus, the clinician and the mother will be blinded.

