### Statistical analysis

Both intention-to-treat and per-protocol analyses will be conducted, following the Consolidated Standards of Reporting Trials (CONSORT) guidelines for randomized controlled trials and will be conducted with the statistician and researchers blinded to group status. The two groups will be described for demographic characteristics and risk factors for perineal pain after episiotomy. The existence of a “ropivacaine effect” (i.e., a difference between the two groups for the primary outcome measure and the secondary outcome measures) will be analyzed. In case of missing data for the primary endpoint, two types of imputation will be realized (multiple imputation and worst case imputation): NPRS strictly superior to 3/10 on the perineal repair area. The percentage of patients with an NPRS strictly superior to 3/10 on the perineal repair area at D7 will be compared between groups (ropivacaine versus placebo) by a mixed effects logistic model in order to take into consideration parity, center, and group as fixed effects. A sensitivity analysis will be performed to consider analgesic administration at H2 and D7. The analgesic consumption will be added in a fixed effects model. A generalized linear mixed regression approach will be used for three criteria: the impact of perineal pain on sexuality (FSFI), depression (EPDS), and quality of life (SF-36) at D7, M3, and M6. This analysis allows taking into account intraindividual and interindividual variability. The group and temporal effects will thus be estimated.

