### Sample size

According to previous research [5, 8, 9], approximately 70% of patients experience perineal pain due to an episiotomy at D7 postpartum. To show a relative reduction of at least 30% in this incidence in the ropivacaine arm with 90% power at the 5% level of significance and a bilateral test, the study requires 124 women with episiotomy in each group. In order to ensure sufficient power in the event of participant dropout, an additional 10% will be recruited. Therefore, a total of 272 patients should be included in the study (136 in both groups).

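### Center and parity, the randomisation strata, are named for the primary model but not for the FSFI, EPDS and SF-36 mixed models; if they are prognostic, omitting them makes those standard errors conservative

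*Protocol article*

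**What the plan says.** The Randomization section of the protocol article fixes the strata: "The randomization will be centralized and stratified by center and parity and will be performed according to a 1:1 ratio". It adds that blocks are of constant size: "The randomization will be performed by nonvarying size block".

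The Statistical analysis section then describes two kinds of model in one paragraph:

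- **Primary outcome (NPRS above 3 at day 7).** The groups are compared "by a mixed effects logistic model in order to take into consideration parity, center, and group as fixed effects". Both strata are in the model.
- **FSFI, EPDS and SF-36 at D7, M3 and M6.** "A generalized linear mixed regression approach will be used for three criteria". The article says that this approach handles variability within and between women, and closes with "The group and temporal effects will thus be estimated". Center and parity are not mentioned.

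The article does not say that group and time are the only terms, and it does not exclude the strata.

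**The concern.** Stratified blocked allocation balances the arms within each center-by-parity cell. Differences between cells therefore contribute almost nothing to the true sampling error of the group effect. A model without center and parity does not know this. It counts their variance as unexplained variation between women and reports a standard error that is too large. A random intercept per woman does not help, because it absorbs the same variance as unexplained.

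At stake are the width of the confidence intervals and the power for quality of life, depression symptoms and sexual function. The Sample size section powers the trial for day-7 pain only and sets no power target for these three outcomes, so precision given away here is not covered by any stated margin.

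**Working it through.** **1. The plan's own figure.** The only calculation in the article is for the primary outcome: "approximately 30% relative risk reduction in the incidence of perineal pain at day 7, from 70.0% to 50.0"%, "with 90% power at the 5% level of significance and a bilateral test". With a pooled variance and no continuity correction:

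n = [1.960·√(2·0.6·0.4) + 1.2816·√(0.7·0.3 + 0.5·0.5)]² / 0.20² = (1.358 + 0.869)² / 0.04 ≈ 124 per group.

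This reproduces the stated 124. Adding 10% gives 136.4, so 136 per group and 272 in total. The article has no corresponding figure for FSFI, EPDS or SF-36, and no standard deviation, intraclass correlation (ICC) or prognostic strength of the strata. What follows is a range under assumptions.

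**2. Formula.** Treat each score as continuous with complete data at three visits. The group effect in a random-intercept model is then a comparison of women's mean scores. Let R² be the share of the variance of a woman's mean score explained by center and parity. Under stratified allocation:

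- ratio of the unadjusted to the adjusted standard error: k = 1/√(1 − R²)
- true two-sided level of the unadjusted test: 2·[1 − Φ(1.96·k)]
- its power where the adjusted model has 80%: Φ(1.960 + 0.842 − 1.96·k)

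| R² (assumed) | k | SE excess | True level | Power |
|---|---|---|---|---|
| 0% | 1.000 | none | 5.0% | 80.0% |
| 5% | 1.026 | 2.6% | 4.4% | 78.5% |
| 10% | 1.054 | 5.4% | 3.9% | 76.9% |
| 15% | 1.085 | 8.5% | 3.4% | 75.0% |

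**3. The scale of R² matters.** The same percentage means different things on other scales. Assume an ICC of 0.5. The variance of a three-visit mean is then 0.5 + 0.5/3 = 0.667 of the per-visit variance, and 0.5/0.667 = 75% of it lies between women.

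- If 5%, 10% and 15% are shares of *between-woman* variance, R² is 3.75%, 7.5% and 11.25%, and the SE excess is 1.9%, 4.0% and 6.1%.
- If r is the share of *per-visit* variance, with an ICC of 0.5 in the remainder, R² = r / [r + 0.667·(1 − r)]. For r = 5%, 10% and 20%, R² is 7.3%, 14.3% and 27.3%, and the SE excess is 3.9%, 8.0% and 17.3%.

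**4. Simulation check.** 4,000 trials per setting were simulated: 272 women, four center-by-parity cells, blocks of 4 (assumed, as the article gives no block size), three visits, complete data, ICC 0.5. The model was fitted with and without center and parity.

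| Share of per-visit variance | SE excess, unadjusted | Type I error, unadjusted | Type I error, adjusted |
|---|---|---|---|
| 0% | 0.0% | 0.054 | 0.054 |
| 1% | 0.8% | 0.050 | 0.051 |
| 2% | 1.6% | 0.052 | 0.055 |
| 5% | 3.8% | 0.043 | 0.050 |
| 10% | 8.0% | 0.033 | 0.049 |
| 20% | 17.3% | 0.023 | 0.051 |

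The Monte Carlo error of a 5% rejection rate is √(0.05·0.95/4000) ≈ 0.3 percentage points. The SE excesses agree with step 3. At 10%, the true sampling SD of the estimate was 0.0929 without adjustment and 0.0927 with it. The estimator is practically the same; only the reported standard error differs.

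**The case against.** The strongest objection is that the article condenses a longer protocol (version 8.0 is named under Trial status). The sentence on group and temporal effects says what will be estimated and is not a covariate list. A reader might infer that the models contain group and time only, and that the strata have been deliberately dropped. The text does not support that: it never says only, and an analysis plan that is not shown may already list center and parity. This stands, and it is why the point is conditional on the models being fitted as described. It does not remove the contrast within one paragraph, which names fixed effects for the primary model, and an added covariate for its sensitivity analysis, but no strata for these models.

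Second, a reader might infer that the standard errors are too wide as a matter of fact. They are so only if center or parity predicts these scores, and the documents give no evidence on that. At 1% or 2% of per-visit variance the excess is 0.8% or 1.6%, and the type I error cannot be told apart from 5%. This also stands.

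Third, one might argue that the primary and secondary models would yield odds ratios conditional on different factors. That would need FSFI and EPDS to be dichotomised in these models. The article gives cut-offs for both scales but does not say that the mixed models will use them, so the argument is not relied on here.

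Finally, the effect is conservative and confined to secondary outcomes. This bears on the weight of the point; it does not make the omission useful.

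**Conclusion.** The point holds in a conditional and modest form. As described, the FSFI, EPDS and SF-36 models do not name the factors on which allocation was balanced, although the primary model does. If they are fitted that way, the standard error of the group effect is conservative to the extent that center and parity are prognostic: by nothing at R² = 0, and by about 2.6% to 8.5% for R² of 5% to 15% of the variance of a woman's mean score. At the upper end of that range, power drops from 80% to about 75%.

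These sizes rest on an assumed R², continuous scores and complete data. The conversions between scales and the simulation also assume an ICC of 0.5, and the simulation assumes blocks of 4. There is no bias in the estimate and no added risk of a false positive. The primary analysis already includes both strata and is untouched.

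**What to change.** In the Statistical analysis section, and in the analysis plan if it does not already say so, state that center and parity enter the FSFI, EPDS and SF-36 mixed models as fixed effects, alongside group, time and the woman-level random effect.

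The cost is one sentence, settled before unblinding, and two degrees of freedom out of about 270 (parity taken as two levels). Both factors are needed to randomise each woman, so no new data, patients or procedures are required. Settling it in advance also removes a later choice between adjusted and unadjusted results.

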### Sample size

According to previous research [5, 8, 9], approximately 70% of patients experience perineal pain due to an episiotomy at D7 postpartum. To show a relative reduction of at least 30% in this incidence in the ropivacaine arm with 90% power at the 5% level of significance and a bilateral test, the study requires 124 women with episiotomy in each group. In order to ensure sufficient power in the event of participant dropout, an additional 10% will be recruited. Therefore, a total of 272 patients should be included in the study (136 in both groups).

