## Abstract

**Background:**

Perineal pain due to episiotomy is commonly reported and can be severe enough to disturb the mother–infant dyad during the postpartum period. Its incidence at day 7 postpartum varies from 63% to 74%. Recent studies have investigated the analgesic efficacy of perineal infiltration of ropivacaine after episiotomy but have only focused on the immediate postpartum period (at 24 and 48 h after birth). Large, adequately powered, multicenter, randomized controlled trials are required to evaluate the impact of ropivacaine infiltration on perineal pain and mid- and long-term quality of life before the widespread use of ropivacaine to prevent perineal pain after episiotomy can be recommended.

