## Background

Episiotomy is a surgical enlargement of the vaginal orifice performed with scissors and requires sutures to be repaired [1]. The midwife or the obstetrician can perform an episiotomy to facilitate childbirth in case of severe fetal heart rate anomaly, and it is occasionally conducted to prevent obstetric anal sphincter injury in vaginal delivery [2]. Considering all maternal consequences of episiotomy, its routine use has been questioned, and restrictive episiotomy policies are recommended by clinical practice guidelines [3]. Despite this restrictive policy, episiotomy is still a common surgical procedure [4].

Perineal pain is a common consequence of episiotomy and affects up to 97% of women on day 1 postpartum [5, 6] and up to 70% of women at days 7 to 10 postpartum [7–9], and it may persist until at least 5 months postpartum [10, 11]. Pain after the perineal wound (apart from episiotomy) is also reported but less studied because of the high variability of the localization and the depth of the tear. Postpartum perineal pain may have a negative maternal impact, can affect the quality of life of the mother, and may be severe enough to disturb the postpartum period and the mother–infant dyad [5, 6]. Symptoms of postpartum depression affect 10–15% of women [12, 13]. An association between persistent perineal pain and symptoms of postpartum depression has been identified by several studies [14, 15]. After adjustment for covariates, an increased risk for depression was shown at 4–6 weeks and 6 months among women who had perineal pain compared with those without perineal pain [16]. In this prospective study, pain at 3–5 days postpartum was a predictor of symptoms of postpartum depression at 3 months [16]. Moreover, a dyspareunia rate of approximately 25% was observed in women who had an episiotomy [17]. Sexual disorders in women with postpartum perineal pain have previously been reported [10, 18, 19]. In addition, a clinical study showed that 12.8% of the women who underwent episiotomy presented with chronic perineal pain at 5 months, which was related to obstetric and postpartum factors (i.e., perineal pain in the first 48 h) [11].

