Ropivacaine is a drug already used in clinical practice for the treatment of acute pain in adults. For example, during childbirth (continuous or bolus epidural infusion), parietal infiltration or peripheral nerve blocks have been reported to be associated with a high rate of decreased pain [24]. Ropivacaine is an anesthetic with longer duration than lidocaine [25]. A complication of infiltration techniques is the systemic toxicity of local anesthetics. This results from large doses of anesthetic administration or from an injection into a space with important systemic resorption. In both cases, this can be prevented with knowledge of the products and injection sites and observing usual precautions when injecting a local anesthetic.

Three studies have already studied the analgesic efficacy of ropivacaine in perineal infiltration after episiotomy [26–28]. Gutton et al. [26] found a significant decrease of pain measured using a visual analogue scale (VAS) at 24 h in a cohort of 102 women in the ropivacaine group (3; 95% CI, 1.5 to 4) versus lidocaine group (4; 95% CI, 2 to 6) (*p* = 0.004). Moreover, the proportion of patients with a VAS ≤ 4 was significantly higher in the ropivacaine group (70.6% versus 43.1%; *p* = 0.009). These results remained at 48 h. In an unblinded study, Sillou et al. [28] compared the injection of ropivacaine in the margin of the episiotomy (*n* = 31) with the absence of infiltration (*n* = 31). The pain evaluated by NPRS was significantly lower in the ropivacaine group at hour 4 (H4) (1.9 ± 0.3 versus 3.6 ± 0.5; *p* = 0,006), H8 (3.3 ± 0.4 versus 5.2 ± 0.4; *p* = 0.003), H12 (2.8 ± 0.4 versus 5.2 ± 0.4; *p* = 0,0001), and H24 (2.6 ± 0.4 versus 4.3 ± 0.4; *p* = 0.006). However, in a cohort of 154 women, Schinkel et al. [27] compared the injection of ropivacaine versus lidocaine versus normal saline serum and did not find differences at 24 h in terms of time to first oral analgesic request (13.9 h versus 17.0 h versus 16.6 h; *p* = 0.104), proportion of patients who did not request oral analgesics (35% versus 54% versus 53%; *p* = 0.09), and VAS score (ropivacaine 16.8 ± 11.6; lidocaine 12.4 ± 9.7; saline 16.2 ± 11.5; *P* = 0.08). These studies focused on 24 and 48 h after childbirth, and no analysis of the mid- and long-term pain levels, dyspareunia, or depression occurrence was conducted. If the mother has less pain at midterm (7–10 days postpartum), it could increase mother–infant interaction and bonding.

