### Outcome measures

#### Primary outcome measure

The primary outcome is the analgesic efficacy of ropivacaine at day 7 postpartum (midterm) measured with the NPRS, strictly superior to 3/10 on the perineal repair area. The systematic use of NPRS will allow an objective measurement of perineal pain in the postpartum period. The NPRS is a simple instrument widely used to assess pain intensity [29]. The patients should rate their pain on a defined scale ranging from 0 to 10, where 0 is no pain and 10 is the worst pain imaginable. This scale has already been used in several studies that assessed perineal pain after episiotomy [28, 30].

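### The 90% power rests on a 70% day-7 rate of perineal pain given without an intensity cut-off, so it is not shown to apply to the primary endpoint of NPRS above 3/10

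*Protocol article*

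**What the plan says.** - **Sample size:** the control rate comes from previous research, in the words "approximately 70% of patients experience perineal pain due to an episiotomy at D7 postpartum". The section then plans a relative reduction of at least 30% in that incidence, with 90% power at a two-sided 5% level. This gives 124 per group, raised by 10% to 136 per group (272 in total).
- **Abstract, Methods/design:** "This study will have 90% power to show approximately 30% relative risk reduction in the incidence of perineal pain at day 7", with the two rates given as 70.0% and 50.0%.
- **Abstract, Background:** an incidence at day 7 between 63% and 74%, with no cut-off. The main Background section likewise says "up to 70% of women at days 7 to 10 postpartum".
- **Primary outcome measure:** the event is an NPRS score "strictly superior to 3/10 on the perineal repair area", on a 0 to 10 scale whose zero point means no pain.
- **Statistical analysis:** "The percentage of patients with an NPRS strictly superior to 3/10 on the perineal repair area at D7 will be compared between groups".
- **Discussion:** the trial is described as adequately powered.

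**The concern.** A woman scoring 1, 2 or 3 on the NPRS has perineal pain but is not a primary-endpoint event. A rate of perineal pain with no stated threshold and a rate of NPRS above 3 are therefore different quantities, and the second cannot exceed the first in the same women. The sample size uses the first kind of figure and the primary analysis tests the second.

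This matters because the effect is planned as a relative reduction. If the placebo rate of the actual endpoint is below 70%, a 30% relative reduction is a smaller absolute difference, and 124 per arm gives less than the stated power. A non-significant result could then be read as evidence of no benefit from an adequately powered trial, although the named effect might well have been missed.

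**Working it through.** **Inputs.** Control rate 70%, ropivacaine rate 50% (Abstract, Methods/design; the 70% also in Sample size). Two-sided 5%, power 90%, 124 per arm, relative reduction of at least 30% (Sample size). Allocation 1:1 (Randomization).

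**Step 1: reproduce the plan.** Two proportions, pooled variance under the null, no continuity correction, with p̄ the mean of the two rates:

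n = [1.96·√(2p̄(1−p̄)) + 1.2816·√(p₁(1−p₁)+p₂(1−p₂))]² / (p₁−p₂)²

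For 0.70 and 0.50, p̄ = 0.60:

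n = [1.96·√0.48 + 1.2816·√0.46]² / 0.20² = (1.358 + 0.869)² / 0.04 = 124.0.

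The stated 124 is reproduced, with power 0.900. From 70% to 50% is a relative reduction of 20/70 = 28.6%; an exact 30% (70% to 49%) would need 113 per arm.

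**Step 2: keep 124 per arm and vary the control rate.** The article gives no day-7 rate of NPRS above 3, so the control rate is an assumption shown over a range.

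Power = Φ{ [ (p₁−p₂)·√124 − 1.96·√(2p̄(1−p̄)) ] / √(p₁(1−p₁)+p₂(1−p₂)) }

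Worked example, 50% against 35% (30% relative), p̄ = 0.425:

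(0.15·√124 − 1.96·√0.48875) / √0.4775 = (1.670 − 1.370) / 0.691 = 0.434, and Φ(0.434) = 0.668.

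| Assumed placebo rate of NPRS > 3 | Power, 30% relative reduction | Power, 28.6% relative (the 70-to-50 ratio) | Power, 20-point difference | Relative reduction that 20 points implies | Relative reduction detectable with 90% power |
|---|---|---|---|---|---|
| 70% | 93% | 90% | 90% | 29% | 29% |
| 63% | 85% | 82% | 89% | 32% | 32% |
| 60% | 81% | 77% | 89% | 33% | 34% |
| 50% | 67% | 62% | 90% | 40% | 40% |
| 40% | 51% | 47% | 94% | 50% | 47% |
| 30% | 37% | 34% | 98% | 67% | 56% |

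The 63% row is the low end of the article's own day-7 range for perineal pain, before any threshold is applied.

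**Step 3: can the article's other figures fix the control rate?** The Background section gives three comparator arms at 24 h:
- Lidocaine arm: 43.1% had VAS of 4 or less, so 100 − 43.1 = 56.9% were above 4. This is a stricter cut than above 3, in an active arm.
- Uninfiltrated arm, 31 women: mean NPRS 4.3 ± 0.4. If 0.4 is a standard error, SD = 0.4·√31 = 2.23, and a normal curve puts about 64% at 4 or more (cut at 3.5). Moving the mean by ±1.96 × 0.4 gives about 50% to 76%.
- Saline arm: "saline 16.2 ± 11.5". On an assumed 0 to 100 scale with normal scores, (30 − 16.2)/11.5 = 1.20, so about 12% exceed 30.

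The main Background section puts pain at up to 97% on day 1 and up to 70% at days 7 to 10, so 24-h values would be expected to sit above day-7 values. The three figures suggest that the day-7 rate of NPRS above 3 may be below 70%, but they range from 12% to 64% and none is a day-7 placebo rate.

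**The case against.** A reader might infer three stronger things, and the article supports none of them.

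1. *That the 70% is known to be the rate of any pain.* It is not. The figure is taken from cited studies that are not at hand, and a cut-off in them cannot be excluded. The article also uses the term perineal pain for its thresholded outcome (Aim, design, and setting; Abstract, Methods/design). What can be said is that no cut-off is stated with the 70%, nor with the similar figures in the abstract and Background.
2. *That the 24-h data show a control rate below 70%.* They do not. VAS above 4 on lidocaine is only a lower bound for the share above 3 in that arm. The 64% depends on an assumed standard error, and its range includes 70%. The 12% depends on an assumed scale.
3. *That the trial could not detect a 30% reduction.* This goes too far. Power is still 77% at a control rate of 57% and 85% at 63%. If the 20-point difference in the abstract is held constant, power stays at about 89% or more. With all 136 per arm observed, an upper bound, a 30% reduction has 85% power at a 60% control rate and 71% at 50%.

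The third argument stands only in part. The Sample size section plans a relative reduction, and a fixed 20 points at lower control rates is a larger relative effect than the article plans or justifies.

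It can also be said that a condensed article may leave the definition of the 70% to the full protocol. That does not remove the point. The article itself claims 90% power and an adequately powered trial for an endpoint whose control rate it never gives.

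**Conclusion.** The point holds as a gap between the power statement and the endpoint. The calculation is correct for 70% versus 50%, but nothing in the article shows that 70% is the placebo rate of NPRS above 3 at day 7. The 90% is therefore conditional on an unstated match of definitions.

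The size of any loss is unknown. It is nil if the cited sources used the same cut-off. Otherwise, with the planned 30% relative reduction and 124 per arm, power runs from about 85% at a 63% control rate down to 37% at 30%. These figures rest on the assumed control rates, a constant relative effect and an unadjusted two-proportion test. The randomization, the endpoint and the primary model remain valid. Severity: should be fixed.

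**What to change.** Enrollment of 272 is complete (Trial status), so the changes are to wording and interpretation:

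1. State the definition, including any cut-off, and the source of the 70%.
2. Restate the power as conditional: 90% holds if 70% of placebo women and 50% of ropivacaine women have NPRS above 3 at day 7, a 28.6% relative reduction. Add power and detectable reduction over a range of lower control rates, as in the table above.
3. Qualify the adequately-powered statement in the Discussion in the same way.
4. Interpret a null result by the confidence interval for the treatment effect, not by the planned power.
5. Optionally, add a supportive analysis of the full 0 to 10 NPRS at day 7. The data are already collected. This is a choice for the analysis plan and its absence is not a fault.

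The cost is a few sentences and one small table, with no extra patients. The downside is that the stated power looks less favourable.
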